## Abstract

**Background:**

Idiopathic scoliosis is a three-dimensional structural deformity of the spine that occurs in children and adolescents. Recent reviews on bracing and exercise treatment have provided some evidence for effect of these interventions. The purpose of this study is to improve the evidence base regarding the effectiveness of conservative treatments for preventing curve progression in idiopathic scoliosis.

**Methods/design:**

Patients: Previously untreated girls and boys with idiopathic scoliosis, 9 to 17 years of age with at least one year of remaining growth and a curve Cobb angle of 25–40 degrees will be included. A total of 135 participants will be randomly allocated in groups of 45 patients each to receive one of the three interventions.

Interventions: All three groups will receive a physical activity prescription according to the World Health Organisation recommendations. One group will additionally wear a hyper-corrective night-time brace. One group will additionally perform postural scoliosis-specific exercises.

Outcome: Participation in the study will last until the curve has progressed, or until cessation of skeletal growth. Outcome variables will be measured every 6 months. The primary outcome variable, failure of treatment, is defined as progression of the Cobb angle more than 6 degrees, compared to the primary x-ray, seen on two consecutive spinal standing x-rays taken with 6 months interval. Secondary outcome measures include the SRS-22r and EQ5D-Y quality of life questionnaires, the International Physical Activity Questionnaire (IPAQ) short form, and Cobb angle at end of the study.

**Discussion:**

This trial will evaluate which of the tested conservative treatment approaches that is the most effective for patients with adolescent idiopathic scoliosis.

**Trial registration:**

NCT01761305

## Background

Adolescent idiopathic scoliosis (AIS) is a three-dimensional structural deformation of the spine and trunk with lateral shift and rotation of the vertebrae [1]. Idiopathic scoliosis with curvature over 10° affects around 3% of children and adolescents. Idiopathic scoliosis occurs in otherwise healthy children and is often diagnosed at the time of the pubertal growth spurt. About one tenth develop a more aggressive variant leading to a more severe deformity of the spine and thorax [2]. By early adulthood, the majority of patients with scoliosis suffer from back pain and if the curve progresses to be very large, even pulmonary dysfunction and psychological distress can occur [3].

In its mild form, idiopathic scoliosis is common and is not treated. In Sweden, screening occurs in school grade 4 (age 10–11) and in grade 7 or 8 (ages 13–14), and it can be estimated that at least 200,000 children are screened yearly by school nurses and physicians. The aim is to find the children with moderate scoliosis. These are often treated with a brace to prevent progression to severe scoliosis. More severe curves are treated with spinal fusion surgery. Surgical complications are few but if they occur, may be devastating, such as paraplegia [4]. The spinal curve is corrected and fused with limitation in mobility as a result.

Several theories propose that during the adolescent period of skeletal growth, bone deformation may occur in the event of vertebral body weakness or an imbalance of muscle forces and joint flexibility [5]. A recent review of literature concerning the association of low bone mineral density and idiopathic scoliosis reported generalized osteopenia and an osteoporosis prevalence of 20–38 percent [6]. Adequate levels of self-mediated physical activity and intake of calcium and vitamin-D is a requirement for normal skeletal growth and development during childhood and adolescence. It is well documented that physical exercise is associated with improvements in not only muscle strength, aerobic fitness and motor development but also bone density which may help decrease the risk of osteopenic related bone deformation [7,8].

Current guidelines from the International Scientific Society on Scoliosis Orthopaedic and Rehabilitation Treatment (SOSORT) recommend physical therapy from curve magnitudes >15° Cobb [9]. Furthermore it is recommended that physical therapy and/or bracing of conservative treatment for AIS be implemented when curve magnitudes of 25-45° are apparent [9]. Surgical intervention for AIS is generally first considered when curve magnitudes reach >50° [10]. A recent systematic literature review of all available literature investigating the effectiveness of physical exercise in the treatment of AIS reported the results of 1 randomised controlled trial, 9 prospective cohort controlled trials, 8 prospective observational cohort studies and 2 retrospective cohort studies [11]. Together, the studies provide an evidence base of limited scientific quality suggesting the efficacy of physical exercise in reducing the scoliosis progression. Improved scientific quality of future research will better define the evidence base effects of physical therapies [12].

A recent literature review investigating the effectiveness of brace treatment of AIS reported the results of two prospective cohort controlled trials and 18 longitudinal case control studies [13]. Together, the existing studies provide an evidence base of limited scientific quality for the efficacy of bracing preventing the progression of scoliosis. Two randomised trials comparing brace treatment with observation only are currently being conducted; NCT00448448 and NCT01370057, registered at http://www.clinicaltrials.gov (accessed at March, 12th, 2013). Another trial from Holland has been terminated due to recruitment difficulties [14].

The on-going randomised trial use a thoracolumbar sacral orthosis worn during 20–23 hours per day as the active treatment. This brace is made of hard plastic and stretches from under the arms to the pelvis. It is custom made and corrects the scoliotic curvature of the spine when worn. The psychological impact when using the brace 20–23 hours per day should not be underestimated. In one study, 27% of the brace treated patients reported that the treatment had a major negative effect on their lives [15], and our clinical impression is that this is one of the reasons to the poor compliance that is often seen. Recently, preliminary data suggested that approximately eight hours of night-time bracing with an over-corrective brace was as effective as bracing during 23 hours per day [16].

Night-time bracing is attractive since you wear the brace a limited amount of time. The brace does not restrict activities during daytime. Our clinical impression is that the psychological concern for a teenager is much less when compared to brace treatment day and night-time, which increases the possibility of good compliance. There have been no controlled studies on night time bracing versus observation only. Several uncontrolled trials have been published, indicating an immediate corrective effect on the scoliosis by the brace [17].

Only one low quality study has compared bracing with physical exercise showing no statistical differences in the reduction or progression of scoliosis curves between the groups [18]. To draw valid conclusions about the effectiveness of conservative treatments for AIS, a randomised controlled trial research design is needed to compare the interventions.

### Aim of study

The primary objective of this study is to improve the evidence base regarding the effectiveness of conservative treatments for preventing the progression of AIS. Secondary aims include improving knowledge of clinical features that may predict a patient's response to each treatment.

### Hypotheses

1. That the use of a night-time brace and adequate levels of self-mediated physical activity is more effective in preventing curve progression than adequate levels of self-mediated physical activity alone.

2. That prescribing scoliosis specific exercise and adequate levels of self-mediated physical activity is more effective in preventing curve progression than adequate levels of self-mediated physical activity alone.

## Methods/design

### Study design

Prospective randomised controlled trial. In total, 135 patients will be randomised into one of three groups. The study design is outlined in Figure 1. The protocol conforms to the CONSORT guidelines for non-pharmacological studies [19] and has been registered on ClinicalTrials.gov, identifier: NCT01761305.

**Figure 1 F1:**
[figure not shown]
Flow chart of the randomised controlled study.

### Study centres

This is currently a single-centre study at Karolinska University Hospital in Stockholm, Sweden. Further study centres may be involved if the recruitment rate is slow. Children and adolescents that are referred to the orthopaedic department for scoliosis will be screened. Individuals that fulfil the inclusion criteria will be asked for participation. After informed consent, randomisation will take place.

### Inclusion criteria

– Diagnosis of idiopathic scoliosis.

– Skeletally immature with estimated remaining growth for at least one year.

– Not more than one year after menarche.

– Primary Cobb angle between 25 and 40 degrees.

– Curve apex T7 or caudal.

– Males and females aged 9–17 years.

### Exclusion criteria

– Scoliosis with a possible non-idiopathic aetiology. Patients will be excluded from the study if the pathogenesis of the scoliosis is not idiopathic, but due to a neuromuscular, neurological, congenital malformation or trauma related comorbidity.

– Previous brace or surgical treatment for scoliosis.

– Inability to understand Swedish.

### Randomisation

Randomisation will be done in a 1:1:1 ratio. A computer generated random numbers table in varying block sizes will be prepared a priori by an independent statistician. To conceal randomisation, the same independent statistician will prepare consecutively numbered, sealed opaque envelopes. The envelopes will be kept in a locked location. The envelope is to be opened in the presence of at least two persons. The original randomisation list will be kept by the independent statistician. One additional copy of the randomisation list is kept in a locked safe at the Karolinska Institutet, and not accessible for the research personnel.

### Blinding

In this study, blinding of patients and therapists for treatment is not possible. However, the randomization status of the participants will not be disclosed to the two physicians who will assess the patient's X-rays after the end of the study.

### Radiology

Standing standard scoliosis images will be performed. If possible, the same equipment will be used at all follow-ups. Anteroposterior or posteroanterior images will be performed depending on the laboratory equipment. The patient is asked to stand comfortably in a relaxed position. For the lateral image the patient is asked to stand comfortably in a relaxed position. The feet are parallel to the screen and beside each other. The right part of the body faces the radiation source. The patient holds his hands on a bar in a position in front of and above shoulder level, so that the arms do not obscure the vertebral column. Shoulder and elbow should be at the same level. The elbows are in a right angle. The hands are to be placed adjacent to one another. The brace is not to be worn during the night before the scoliosis images are taken. In addition, skeletal age will be determined from a conventional x-ray of the hand.

### Intervention groups

#### ***Group 1: adequate self-mediated physical activity***

Instructions for self-mediated physical activity will be delivered during an individual 1 hour session. Patients are encouraged to perform the self-mediated physical activities of moderate intensity at least 60 minutes daily, for the entirety of the study. Reinforcement of the assigned intervention will be performed in conjunction with reassessment every 6 months. A training diary will be implemented to follow and motivate the patient's compliance to the intervention protocol.

#### ***Group 2: scoliosis specific exercises***

In addition to receiving the same intervention as group 1, patients will learn how to perform a 3 dimensional self-mediated correction of their scoliosis, muscular stabilization of the corrected posture, and how to perform these postural correction strategies in their activities of daily living [20]. Additional self-mediated hyper-corrective exercises are to be performed with a dosage of 10 repetitions of 30 second isometric holds daily. The scoliosis specific exercises cover similar concepts and methods described in previous literature [21]. The intervention will be delivered to the patient individually by experienced physiotherapists in 3 × 90 minute sessions, once per month during the first 3 months and then every 6 months thereafter. Additional single bolus sessions may occur when extra education is required to master the program. Reinforcement of the intervention will be performed in conjunction with reassessment every 6 months. A training diary will be implemented to follow and motivate the patient's compliance to the intervention protocol.

#### ***Group 3: hyper-corrective night-time brace***

In addition to receiving the same intervention as group 1, a hyper-corrective brace will be worn 8 hours per night. The brace will be specifically designed to provide a 3 dimensional hyper-correction of the patient’s individual scoliosis type. Reinforcement of the assigned intervention will be performed in conjunction with reassessment every 6 months. A training diary will be implemented to follow and motivate the patient's compliance to the intervention protocol. The spine orthotist is available for brace adjustment when needed.

Patients in all groups are also be recommended 4 standard servings of dairy (or equivalent non-dairy substitute) daily to guarantee recommended daily intake of calcium and vitamin-D.

An additional file shows the content of the interventions this in more detail [see Additional file 1].

### Non-participants

Patients not willing to participate in the study will be offered the standard care of treatment, which in our institution is a corrective thoraco-lumbar sacral orthosos (TLSO) bracing for at least 20 hours per day. Patients not willing to participate in the study will be asked to fill in the same questionnaires as the study cohort at the time when treatment is suggested. The radiological and clinical result of these patients will be obtained from the regular orthopaedic files and radiographs taken.

### End of study

The study will be terminated when the participant reaches skeletal maturity, defined as less than 1.0 cm growth of body height in 6 months, or if the curve progresses more than 6 degrees, compared to the primary x-ray, seen on two consecutive spinal standing x-rays taken with 6 months interval. Patients who have a progression of the Cobb angle of more than 6 degrees and ultimately reaching the end point failure of treatment will not remain in the study but will be offered a TLSO brace treatment if indicated. In the event that a Cobb angle surpasses 50 degrees, patients will be offered surgical treatment. Post-treatment follow-up is planned to occur at 2, 5 and 10 years prospectively.

### Ethical permit

The trial has received ethical approval from the Regional Ethics Committee in Stockholm, Sweden (Dnr:2012/172-31/4).

### Outcome measures

The patients will be followed up every 6 months for the entirety of the study.

#### ***Primary outcome measures***

• The primary outcome variable, failure of treatment, is defined as progression of the Cobb angle more than 6 degrees, compared to the primary x-ray, seen on two consecutive spinal standing x-rays taken with 6 months interval [22].

#### ***Secondary outcome measures***

• SRS-22r quality of life questionnaire [23].

• International Physical Activity Questionnaire (IPAQ) short form [24].

• EQ5D /-Y/ quality of life questionnaire [25].

• A modified Spinal Appearance Questionnaire [26].

• Cobb angle at end of the study.

At each 6 month follow-up additional questions regarding protocol fulfillment (According to CONSORT guidelines) [19], patient satisfaction and adverse effects will be asked. Body height and weight will be measured at baseline and at all follow-ups.

### Sample size

Based on figures from previous literature, a failure rate of 45% in the self-mediated physical activity group and a 15% failure rate in the brace and scoliosis specific exercise groups is hypothesised. Given a significance level of 5%, a power of 80% and consideration for dropout of up to 20%, an estimated 45 patients are required in each of the intervention groups.

### Data integrity

The integrity of trial data will be ensured by regularly monitoring of data sheets for omission and errors. Data will be double entered and the cause of any inconsistencies will be rectified. A minimum of 50% of the intervention quota is required to be fulfilled to be considered a compliant intervention.

### Data analysis

Data from the different groups will be compared based on the 'intention to treat' principle. An intention to treat (ITT) analysis means that all patients, regardless of noncompliance, loss to follow-up or drop-out, remain in the analysis of the group to which they were randomised [27]. Multiple imputation of missing data will be used in the ITT analysis. A sensitivity analysis will be performed comparing the ITT data against a per-protocol data exclusively from patients who complied with the study protocol. If a patient in the study receives full-time bracing or surgery due to treatment failure, the Cobb angle at the moment of commencing this treatment will be considered in the secondary outcome analysis of Cobb angle.

Categorical parameters will be compared by the Chi-square test. Continuous and discrete parameters will be measured using parametric or non-parametric tests (depending on skewness) for group comparisons. Individual variables will be tested for their association with treatment effect by adding a predictor × treatment group interaction term to a regression equation. Additionally, Kaplan-Meier survival analyses will be used to display the probability of more than 6 degree Cobb progression over time for each group.

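### End-of-study Cobb angle and questionnaire scores are to be compared by tests chosen from the data's skewness, with no baseline term named; a baseline-adjusted model fixed in advance would be more precise

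*Protocol article*

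**What the plan says.** The Data analysis section sets one rule per type of variable. For categorical variables: "Categorical parameters will be compared by the Chi-square test". By its type, the binary primary outcome (failure of treatment) falls under this rule. For the rest: "Continuous and discrete parameters will be measured using parametric or non-parametric tests (depending on skewness) for group comparisons". That covers the end-of-study Cobb angle and the questionnaire scores listed under Secondary outcome measures.

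Neither rule names a baseline covariate. Regression appears only for testing predictor-by-treatment interactions, and Kaplan-Meier curves only for display. The same section also states: "Multiple imputation of missing data will be used in the ITT analysis".

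Baseline information is available. Inclusion criteria require an entry Cobb angle of 25 to 40 degrees, so every patient has one. Under Non-participants, those who decline are asked to complete the study cohort's questionnaires when treatment is suggested, which implies that the cohort has baseline scores. Under Radiology, "skeletal age will be determined from a conventional x-ray of the hand", but the section does not say at which visit.

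**The concern.** A final Cobb angle is the entry angle plus whatever change followed. Eligible entry angles differ by up to 15 degrees. A comparison of final angles that leaves out the entry angle treats that spread as noise, although it was known before randomisation. The same applies to any questionnaire score with a baseline value.

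Choosing the test from the observed skewness adds a second weakness. A t-type test concerns means and a rank test concerns distributions, so the effect being estimated depends on data that will already have been seen. The absence of a skewness threshold is not the complaint, since an analysis plan could supply one. The complaint is that the article makes the choice depend on the data at all.

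At stake is precision on the secondary outcomes in a trial of 45 per arm, and possibly a modest amount of power on the primary outcome.

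**Working it through.** **1. The plan's own sample size.** Inputs from Sample size: "a failure rate of 45% in the self-mediated physical activity group", against 15% in each of the other two arms; 5% significance; 80% power; dropout of at most 20%. Two-sided testing is assumed, as the article does not state it. With pooled variance and no continuity correction:

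n = [1.960 × √(2 × 0.30 × 0.70) + 0.842 × √(0.45 × 0.55 + 0.15 × 0.85)]² / 0.30² = (1.270 + 0.515)² / 0.09 ≈ 35.4, so 36 per arm.

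36 / 0.80 = 45, the stated figure. At 36 per arm the formula gives the unadjusted comparison 80.7% power.

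**2. Continuous outcomes.** If baseline and final values correlate at r within arms, ANCOVA multiplies the variance of the treatment difference by 1 − r². Take an effect that the unadjusted test detects with 80% power (0.66 SD at 36 per arm). Adjusted power is then Φ(2.802 / √(1 − r²) − 1.960).

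| r (assumed) | Variance factor, ANCOVA | Variance factor, change score, 2(1 − r) | Power, ANCOVA | Gain (points) |
|---|---|---|---|---|
| 0.2 | 0.96 | 1.60 | 81.6% | 1.6 |
| 0.3 | 0.91 | 1.40 | 83.6% | 3.6 |
| 0.5 | 0.75 | 1.00 | 89.9% | 9.9 |
| 0.7 | 0.51 | 0.60 | 97.5% | 17.5 |

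The change-score column is included because the article does not say whether final values or changes will be compared. ANCOVA has the smaller variance in every row.

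Which r is plausible is not documented. As an illustration only, suppose that entry angles are uniform on 25 to 40 degrees (SD 15/√12 = 4.33) and that change is unrelated to entry angle. Then r = 4.33 / √(4.33² + s²), where s is the SD of change. For s = 5, 6, 8 and 10 degrees, r is 0.65, 0.59, 0.48 and 0.40. A tighter spread of entry angles would lower these values.

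**3. Primary outcome.** Simulation of 36 v 36 patients, 4,000 trials per scenario, with marginal failure rates held at 45% and 15% and one normally distributed covariate. The test is the chi-square or the likelihood-ratio test from a covariate-adjusted logistic model.

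| Covariate odds ratio per SD (assumed) | Chi-square | Adjusted, 1 covariate | Gain (points) |
|---|---|---|---|
| 1.0 | 81.6% | 81.9% | 0.3 |
| 1.5 | 81.1% | 82.4% | 1.4 |
| 2 | 81.8% | 85.1% | 3.3 |
| 3 | 81.5% | 87.8% | 6.2 |

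Gains are taken before rounding. The Monte Carlo error of each power is √(0.82 × 0.18 / 4000), about 0.6 points. With three further, useless covariates the gains are −0.6, 0.4, 2.9 and 4.8 points. Taken together: about 0 to 1 point at 1.5, 3 at 2, and 5 to 6 at 3. A test on the standardised risk difference behaves almost identically (within 0.4 points).

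**4. The price.** Expected failures per pairwise comparison are 36 × 0.45 + 36 × 0.15 = 21.6. Under the null (30% in both arms, covariate odds ratios from 1 to 5), the likelihood-ratio test rejected in 5.5 to 5.8% of trials with one covariate and 5.6 to 7.2% with four. The chi-square rejected in 4.7 to 6.0% (Monte Carlo error about 0.35 points). A Wald test with a weak covariate had slightly less power than the chi-square (about 79 to 81%).

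The adjusted odds ratio also changes meaning. The planned rates give a marginal odds ratio of (0.15/0.85) / (0.45/0.55) = 0.216. When the covariate has an odds ratio of 3 per SD, the conditional value is 0.156.

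**The case against.** The strongest reply is that nothing here is wrong. An unadjusted comparison is valid under randomisation, the chi-square reproduces the stated sample size, and Randomisation names no stratification factor that would oblige adjustment. This stands in full for the primary outcome. That endpoint is also defined as progression from the entry x-ray, so each patient's starting angle is already built into it.

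A reader might infer that strong predictors are being ignored and that adjustment is free. The article supports neither. It gives no prognostic strength for any variable, and Aim of study makes learning which features predict response a secondary aim. Eligibility narrows the spread of curve size and remaining growth. Step 4 shows that adjustment has a cost.

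A reader might also infer that chance imbalance biases the primary result. A factor present in half the patients differs by more than 10 points between two arms of 45 with probability about 34% (SD √(2 × 0.25/45) = 10.5 points). That is ordinary sampling variation, already covered by the test's error rate and the confidence interval.

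Multiple imputation does not rule out the chi-square either. Combination rules for such statistics exist, and an unadjusted risk difference pools by Rubin's rules.

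Finally, a condensed article may leave covariates to an analysis plan, and a parametric test could be read to include a baseline-adjusted model. That softens the point but does not remove it. The article does commit to letting skewness choose the test, and it uses regression only for interactions.

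**Conclusion.** The point holds for the continuous secondary outcomes, as a loss of efficiency together with an avoidable data-dependent choice of test. The gain from adjustment is about 2 to 4 power points at r = 0.2 to 0.3, 10 at 0.5 and 17.5 at 0.7, starting from 80%. It rests on an assumed r and on a linear relation between baseline and final value.

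For the primary outcome, adjustment is an optional improvement worth between nothing and about 6 points over covariate odds ratios of 1 to 3 per SD, which are also assumed. The documents do not support calling the primary test wrong, biased or underpowered on this ground.

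**What to change.** - **End-of-study Cobb angle, and questionnaire scores with a baseline value:** prespecify a linear model with treatment arm and the baseline value, to be used whatever the skewness. Report adjusted mean differences with 95% confidence intervals for brace plus activity v activity and for exercise plus activity v activity. Keep the unadjusted tests as supportive.
- **Primary outcome (optional):** prespecify a logistic model with arm and at most two baseline covariates: entry Cobb angle, and skeletal age if the hand x-ray is taken at baseline. Report a standardised risk difference with its 95% confidence interval, pooled over imputations by Rubin's rules. Keep the chi-square as supportive.
- **Timing:** state when skeletal age is determined, so that its use as a baseline covariate is clear.

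The change is to analysis wording only and needs no more patients. Entry Cobb angle is already measured; a baseline skeletal age depends on the timing just mentioned. The statistical price is a type I error for the adjusted primary test that may lie slightly above 5%, which is why the covariates must be few and fixed in advance.

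### The questionnaires are collected every 6 months, but the tests named for them use neither the baseline score nor the repeated visits, and no visit is fixed although follow-up length will differ by arm

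*Protocol article*

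**What the plan says.** All references are to the protocol article.

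- **Collection.** The abstract (Methods/design) states: "Outcome variables will be measured every 6 months". The Outcome measures section says the same of visits: "The patients will be followed up every 6 months for the entirety of the study".
- **Time point.** Under Secondary outcome measures the SRS-22r entry reads only "SRS-22r quality of life questionnaire". The entries for IPAQ, EQ5D-Y and the appearance questionnaire likewise name no visit. The radiographic entry does: "Cobb angle at end of the study".
- **Length of follow-up.** It varies by patient: "Participation in the study will last until the curve has progressed, or until cessation of skeletal growth". Under End of study, patients who reach confirmed failure "will not remain in the study but will be offered a TLSO brace treatment if indicated".
- **Analysis.** Data analysis gives one sentence for these outcomes: "Continuous and discrete parameters will be measured using parametric or non-parametric tests (depending on skewness) for group comparisons". Regression is named only for predictor-by-treatment interactions, and Kaplan-Meier curves only for progression. Multiple imputation is planned for the intention-to-treat analysis. There is a rule for the Cobb angle of patients who go on to full-time bracing or surgery, but none for their questionnaire scores.

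**The concern.** A test chosen by skewness is, on its ordinary reading, a t-test or analysis of variance, or its rank-based counterpart. It takes one value per patient. With 6-monthly scores and exit that depends on outcome, such a test leaves open which value is used, and each choice has a cost:

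- **Last score:** failures are measured when they leave and the others at maturity, and the mix differs by arm.
- **One fixed visit:** the other visits contribute nothing.
- **Each visit in turn:** this gives a series of separate tests, on an increasingly selected sample after month 12.

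Under any of these, the baseline score is unused unless a further step is added. At stake is the randomised evidence on the burden of treatment. The Background and Discussion argue for night-time bracing partly because it should trouble a teenager less than full-time bracing. A comparison with little power, or with a visit chosen after the data are seen, would inform that poorly.

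**Working it through.** **1. The plan's own figure.** Inputs from Sample size: failure 45% v 15%, 5% significance (taken as two-sided), 80% power, 20% dropout. With a pooled variance and mean proportion 0.30:

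n = [1.96 × √(2 × 0.30 × 0.70) + 0.8416 × √(0.45 × 0.55 + 0.15 × 0.85)]² / 0.30² = 35.4, so 36 per arm; 36 / 0.80 = 45.

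This reproduces the stated 45 per arm and gives 36 evaluable patients per arm for what follows.

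**2. Precision.** Assumptions (the article gives no figures): equal correlation ρ between any two scores of a patient, ρ = 0.3, 0.5 or 0.7; a true difference of 0.5 SD, the same at months 6 and 12; two-sided 5% for each active arm against group 1; normal approximation. Relative variance v of one patient's contribution:

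- single unadjusted score: v = 1
- single score adjusted for baseline: v = 1 − ρ²
- mean of two visits adjusted for baseline: v = (1 + ρ)/2 − ρ²

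Power = Φ(0.5 / √(2v/36) − 1.96). Smallest difference detectable with 80% power = 2.80 × √(2v/36).

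| Analysis | v (ρ = 0.3 / 0.5 / 0.7) | Detectable difference, SD | Power for 0.5 SD |
|---|---|---|---|
| Single score, unadjusted | 1 | 0.66 | 56% |
| Single score, baseline-adjusted | 0.91 / 0.75 / 0.51 | 0.63 / 0.57 / 0.47 | 60 / 69 / 84% |
| Mean of months 6 and 12, baseline-adjusted | 0.56 / 0.50 / 0.36 | 0.49 / 0.47 / 0.40 | 81 / 85 / 94% |

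**3. Where the gain comes from.** For a contrast at month 12 alone, the month-6 score adds almost nothing beyond baseline adjustment. The variance ratio is 1.00 with complete data, and 0.99 / 0.98 / 0.97 if 20% miss month 12 but have month 6. The gain needs both the baseline term and the average. Averaging without baseline has v = (1 + ρ)/2 = 0.65 / 0.75 / 0.85 and power 75 / 69 / 63%.

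**4. Sensitivity to a growing effect.** If the difference were 0.25 SD at month 6 and 0.5 SD at month 12, the average would be 0.375 SD. Putting 0.375 into the formula gives 57 / 61 / 76%, below the 60 / 69 / 84% of a baseline-adjusted month-12 contrast.

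**5. Timing of a last score.** Failure must be seen on two consecutive films 6 months apart, so the earliest confirmed failure is at month 12. Take a constant failure probability h per visit from month 12 and, as one assumed case, maturity at month 24 for everyone. Then 1 − (1 − h)³ equals the failure rate:

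- activity-only arm: h = 1 − 0.55^(1/3) = 0.181; mean last visit = 24 − 12 × 0.181 − 6 × 0.148 = 20.9 months
- active arm: h = 1 − 0.85^(1/3) = 0.053; mean last visit = 24 − 12 × 0.053 − 6 × 0.050 = 23.1 months

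The gap is 2.1 months before rounding. Simulation with other assumed maturity times:

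| Maturity | Activity only | Active arm | Gap (months) |
|---|---|---|---|
| Even over 12–24 months | 16.0 | 17.4 | 1.4 |
| All at 24 | 20.9 | 23.1 | 2.1 |
| Even over 12–36 | 20.0 | 22.8 | 2.8 |
| Even over 18–48 | 26.8 | 31.1 | 4.3 |

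With an assumed drift in score of 0.1 to 0.3 SD per year, the shift runs from 0.1 × 1.4/12 = 0.01 SD to 0.3 × 4.3/12 = 0.11 SD.

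**6. Month 12 as the limit.** Failure cannot remove anyone before month 12. By month 18 it has begun to: in the 12–36 case 65% of the activity-only arm and 76% of an active arm are still observed.

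**The case against.** The strongest objection is that the sentence is generic. Repeated-measures tests are also parametric or non-parametric, and a condensed article may leave the visit and the model to a fuller document. A reader might infer that the trial will discard the repeated scores or compare last visits. The article says neither, and that reading is not supported. What remains is that the article does state a method for these outcomes, that the method as ordinarily understood uses neither baseline nor repeated scores, and that the Cobb angle received a time point and a rule for failures while the questionnaires received neither.

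Second, a reader might infer serious bias from unequal timing. The article gives no interval between failure and maturity, and the shift computed above is probably small. This part of the objection stands.

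Third, end-of-participation quality of life is a legitimate target, parallel to the Cobb endpoint, and month 12 is not free of exits. Dropout and early maturity can come first, although entry requires at least a year of estimated remaining growth. This also stands, so the end-of-participation comparison should be kept.

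Fourth, choosing the test by skewness gives some protection that a linear model alone would drop. That is fair and is met by a robustness check.

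Finally, both hypotheses concern curve progression only, so the point must not be read as touching the primary result.

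**Conclusion.** The concern holds as a choice of analysis that can be improved at almost no cost. It is not an error in the trial's main result: the primary analysis and 45 per arm are unaffected.

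The main ground is precision: about 56% power for a 0.5 SD difference with a single unadjusted score, against about 81% to 94% with the baseline-adjusted 6- and 12-month average. This rests on assumed correlations of 0.3 to 0.7, 36 evaluable patients per arm, no multiplicity adjustment and an equal difference at both visits. It also presumes a baseline questionnaire in randomised patients. The article implies one, since non-participants complete the same questionnaires when treatment is suggested, but does not state it outright.

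The timing gap of about 1 to 4 months is a secondary ground and arises only if last scores are compared. The unfixed visit matters chiefly because it leaves room to choose one after the data are seen.

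**What to change.** Before the outcome data are examined by arm, replace the simple tests for the questionnaire scores with a baseline-adjusted repeated-measures model: arm, visit, arm × visit, baseline score, and within-patient correlation.

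- **Main contrast:** the average of the 6- and 12-month scores, each active arm against group 1.
- **Supportive:** the separate month-12 contrast, later visits, and the end-of-participation comparison. State that estimates beyond month 12 rest on a missing-at-random assumption after failure exit.
- **Missing data:** say how the planned multiple imputation treats scores after failure exit.
- **Skewed scores such as IPAQ:** add a rank-based or bootstrap check.
- **Baseline:** confirm that randomised patients complete the questionnaires before treatment starts.

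The cost is a few sentences in the analysis plan and slightly more analysis work, with no extra patient or visit. The downside is that the main contrast describes quality of life in the first year rather than at the end of treatment, and it loses power if differences emerge only late.
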